### Recruitment {15} and Consent {26}

Pathways into the trial have been defined collaboratively with Parent Collaborators, local authority partners in Glasgow and Bromley and the IPS teams (Fig. 2). This collaborative approach ensures that recruitment into the sample is representative of our target population, in terms of social class, ethnicity, gender, sexuality and disability. Our recruitment and retention strategy builds upon a highly successful approach used in our ongoing BeST^?^ trial, employing experienced social work-trained Recruitment Coordinators [99]. The trial recruitment coordinators (RCs) will work with organisations to identify the target population, facilitate referrals to the study, and screen for eligibility. Parent collaborators will also be instrumental in supporting all participants throughout the research process, including any who withdraw.

Potential participants may be identified by social workers (and other support services via a social worker) who will conduct the initial eligibility assessment and provide families with the study participant information leaflet explaining the study, its intent, and what participation would entail. With the family’s consent, their details will be passed onto the RCs who will talk to the interested families to discuss the study further, answer any questions and, if proceeding, go through the informed written consent process. Consent to access routinely collected health and social work data about the child and parent will also be sought, to test the feasibility of collecting data on service/intervention delivery for each arm.

The research nurse (see below) will contact Consenting families and invite them for baseline research assessments (Table 2). Once this is complete, they will be randomised to IPS or services-as-usual. Families will be given the option of assessments taking place remotely or face-to-face. The flow of participants through the study is shown in Fig. 2. An online system will collect eligibility screening data for referrals, providing data on eligibility rates, any ambiguities regarding eligibility criteria, reasons for ineligibility, and non-participation. This will also alert the research team to situations when referral and/or recruitment rates fall below expectations to allow remedial actions if required. After randomisation, the RC will pass the referral information to the IPS Team Managers, and the IPS Family Engagement Worker will contact the family to commence assessments. In both arms of the trial the RC will inform the family and SW of randomisation outcome (see below).

For the process evaluation, all parents taking part in the study will be invited to participate in a semi-structured interview. These will be conducted in a separate session at a mutually convenient time and place, by virtual or face to face methods. These interviews will be optional, and a member of the research team will take written informed consent separately. Participants will receive a voucher for taking part in research interviews. In relation to parent collaborators and IPS and services as usual practitioners, informed consent will be taken prior to conducting any interviews or focus groups. It will be emphasised that participation is voluntary, and data will be anonymous. Only the researcher conducting the process evaluation will know which members of the teams will and will not participate.

### Assignment of Interventions: Allocation {16} and Blinding {17}

After informed consent, verification of inclusion/exclusion criteria, and completion of baseline measures, participants are stratified by site (Bromley or Glasgow) then individually randomized within site to either IPS or SAU (1:1) via computer-generated randomization through www.graphpad.com. Once a family has completed their baseline assessments, the recruitment coordinator (RC) will notify the trial manager, who will then confirm the assigned trial arm via email. During the feasibility stage, the randomisation sequence will have been predetermined and securely recorded, accessible only to the trial manager. This process will ensure allocation concealment, preventing prediction or influence on group assignments. The RC will then inform the family and referrer of the randomisation outcome via telephone, text, or email. The study will follow a single-blind design: participants and providers will be aware of the treatment allocation after baseline assessments, whereas researchers conducting baseline and follow-up assessments will remain blinded. To maintain blinding integrity, researchers will follow a scripted protocol when conducting assessments, as in the BeST^?^ Trial. Additionally, at the end of the trial, researchers will state which intervention they believe parents received to assess the effectiveness of blinding.

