#### Family Engagement Works and Family Engagement Leads

Our early co-production work highlighted the need for a Lived Experience workforce to help bridge the gap between IPS and the families that will use the service. As a result, the IPS teams will include two Family Engagement Workers (FEW) and a Family Engagement Lead. The Family Engagement Worker, informed by their own experiences of working with services, will work alongside families as they are randomised into IPS, discussing the intervention, seeking informed consent, arranging appointments (which could include preference for home visit or office appointments, transport/childcare needs, and identifying any learning, language, or cultural needs) and conducting some of the early assessments with families. In particular, the FEW will enhance the relationships between professionals (e.g., social workers and clinicians) and families through working with parents and caregivers, to promote choice and opportunities to enable families to feel connected and valued in their assessment and support plan. Family engagement is tailored to meet the local needs of families and support their connections with other helpful networks and services.

The Family Engagement Lead will ensure FEWs are fully supported to deliver safe, quality interventions with families within the wider team, and ensuring that decisions and practices are informed by lived experience at all levels. Their role will be to recognise and consciously work to remove barriers for the Lived Experience workforce, including practical constraints, attitudes/workplace culture, and bureaucratic processes that restrict effective and authentic Lived Experience work. Following the development phase establishing the need and readiness for this feasibility trial, this paper now outlines the protocol for the feasibility trial of IPS.

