***Professional-based measures***						
Professional Focus group Parent Collaborator Focus group / interview	RA RA					✔ (+ as required) ✔ (+ as required)

Key: ^1^Consent will take place a minimum of 24 h after information has been presented to families

*SW* Social worker, *RC* recruitment co-ordinator, *TM* trial manager, *RN* research nurse, *RA* research associate, *FEW* family engagement worker, *b-CAP* Brief Child Abuse Potential Inventory, b-CAP, *SDQ* Strengths and Difficulties Questionnaire, *ITSEA* Infant–Toddler Social & Emotional Assessment, *PEDs-QL* Paediatric Quality of Life Inventory, *GHQ-12* General Health Questionnaire, *ICECAP-A* ICEpop CAPability measure for Adults, *PROM* parent-reported outcome measure, *PREM* parent-reported experience measure

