##### Parent-Reported Outcome Measure and Parent-Reported Experience Measure

In addition to the validated outcome measures described above, an important output of our earlier co-production and qualitative process evaluation work was the development of a parent-reported outcome measure (PROM) and parent-reported experience measure (PREM) to capture outcomes and experiences that are salient to our families when engaging with social care. These measures will be piloted with families in the current study and completed with the researcher and lived experience lead.

PROMs have been successfully used in healthcare to inform shared decision-making and to tailor care to individual needs, and are increasingly used in randomised controlled trials to examine whether an intervention is effective and cost-effective from the perspective of service-users [91]. PREMS are used to examine patients’ experiences of healthcare and examine factors such as empathy and respect [92]. Although the role of PROMs and PREMs in health care is increasingly being recognised, to our knowledge this will be the first time PROMS and PREMS have been developed for a social care context. In line with the theoretical basis for this study that highlights how stigma, shame, and structural inequalities are key problem drivers, and that respect, reduction in shame, and development of trust are crucial in allowing relationship-focused interventions to be effective, we believe that development of these new tools will be essential. The data from the PROM and PREM will also feed into the economic evaluation (see below).

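### Table 2 lets IPS team staff who know the allocation collect the PROM and PREM at follow-up, so the single-blind statement does not hold for these two measures as written

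*Protocol article*

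**What the plan says.** The section on allocation and blinding divides people into two groups. On one side, "participants and providers will be aware of the treatment allocation after baseline assessments". On the other, "researchers conducting baseline and follow-up assessments will remain blinded". It adds that assessors follow a script and that, at the end of the trial, they guess each parent's arm as a test of blinding.

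Table 2 (Study Procedures) gives RA/FEW as the staff for both the PREM and the PROM and ticks both at baseline and at the 3/6-month follow-up. The key expands FEW as "family engagement worker".

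The section on Family Engagement Workers and Leads states that "the IPS teams will include two Family Engagement Workers (FEW) and a Family Engagement Lead". It describes the FEW as someone who "will work alongside families as they are randomised into IPS, discussing the intervention, seeking informed consent, arranging appointments", and who also carries out some early assessments. Under Recruitment and Consent, once a family is randomised to IPS, "the IPS Family Engagement Worker will contact the family to commence assessments".

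The section on the PROM and PREM describes collection differently: the measures are "completed with the researcher and lived experience lead".

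**The concern.** A reader would take the single-blind statement to cover every follow-up questionnaire. For two of them, the table permits collection by staff who deliver one of the arms.

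The PREM is where this matters most. The article says that such measures look at matters like empathy and respect, and its theory of change rests on respect, trust and reduced shame. It also reports that parents involved with social services often feel powerless and fear that asking for help could lead to their child being removed. If child protection proceedings are needed, what IPS has learned is to inform recommendations to social care. A parent in IPS who completes the PREM with an IPS worker therefore has reasons to answer cautiously or favourably. A parent in SAU completing it with the same worker would not be rating that worker's own service.

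Two uses of the data are at stake. Acceptability and feasibility of the PROM and PREM form a secondary outcome here, with an amber criterion in Table 1, and acceptability learned with a FEW's help may not carry over to independent collection. The data also feed the economic work, and the Discussion plans to use both measures in the definitive trial to judge effectiveness and cost-effectiveness from the parents' perspective.

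**Working it through.** No figure in the plan bears on this point and there is nothing to recompute. The check sets the sections side by side.

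1. **Is the blinding claim general?** Yes. The allocation and blinding section covers follow-up assessments without naming or excluding any measure, and no other section exempts the PROM or PREM.

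2. **Are FEWs providers or researchers?** They sit in the IPS teams, discuss the intervention with families, arrange appointments and begin assessments after randomisation. By the article's own division they are providers.

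3. **Can a FEW be blind at follow-up?** No. FEWs take up families because those families were randomised to IPS. The end-of-trial guess of allocation would tell nothing about blinding for them.

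4. **Does the table allow a FEW to collect at follow-up?** Yes. RA/FEW is entered for both measures and the follow-up column is ticked. The slash does not say whether it means either or both, and nothing limits the FEW to one time point or one arm.

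5. **Does the text on the measures settle it?** No. It names the researcher and the lived experience lead. The co-production section describes that lead as a co-investigator, and the article does not say that this person is a FEW. The two descriptions differ, and neither is marked as taking precedence.

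6. **Which time point is affected?** Follow-up only. Baseline assessments are completed before randomisation, so there is no allocation to conceal at that stage.

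7. **How much of the assessment is affected?** Table 2 gives the research nurse seven questionnaires: b-CAP, SDQ, ITSEA, PedsQL, the Demographic and Service Use Questionnaire, GHQ-12 and ICECAP-A. Adding the PREM and PROM gives 7 + 2 = 9. Two of the nine are affected.

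Steps 1 to 4 establish the contradiction. Step 5 shows that the article does not resolve it elsewhere.

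**The case against.** The strongest reply is that RA/FEW may be a loose label. The section devoted to the measures does not mention FEWs, and the arrangement it gives may be the intended one. That is possible, and it is why the point is an inconsistency to reconcile and not a finding that FEWs will collect the data. But a site working from Table 2 could properly send a FEW.

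A second reply is that the blinding sentence speaks of researchers, and a FEW is not one. On that reading the sentence is literally true, but a follow-up assessment is then done by someone the article itself calls unblinded, and the single-blind description still fails for that measure.

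A third reply has real weight. Parents know their arm and report on themselves, so a blinded administrator would not remove arm-related reporting. All instruments are on Qualtrics and assessments may be remote, so a parent need not answer in front of a worker. The plan for putative measures is means and standard deviations, no between-arm test of the PROM or PREM is described, and lived-experience support in completing them looks deliberate. This limits the consequence to a risk of one-sided answers and to the transferability of the acceptability findings.

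Some stronger inferences are tempting but unsupported:

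- **Blinding broken at baseline.** It cannot be, since baseline precedes randomisation.
- **SAU families contaminated by contact with a FEW.** Nothing says that IPS content would be delivered while a questionnaire is completed.
- **Every IPS family assessed by a FEW, or a bias of a given size.** The entry RA/FEW does not show the former, and no figure in the article supports the latter.
- **The research associate as an equally unsuitable collector.** The follow-up interview asks about randomisation, but interviews are held in a separate session, so this depends only on which comes first.

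**Conclusion.** The point stands as a contradiction within the article. At the 3/6-month follow-up, Table 2 permits unblinded IPS staff to collect the PROM and PREM, the blinding section says follow-up assessors are blinded, and the section on the measures names other people. The single-blind statement is therefore wrong as written for these two measures.

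The contradiction follows from the text alone. The risk of socially desirable answers in the IPS arm assumes that a FEW is in fact used and that the parent is aware of the FEW's part in completing the form. Its size cannot be estimated from the documents.

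Severity is moderate. Recruitment and retention, which form the primary outcome, do not depend on who administers these forms. The b-CAP, planned as the principal outcome of the definitive trial, and the other research-nurse measures are untouched.

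**What to change.** Remove FEW from the PROM and PREM rows of Table 2. Name one administrator who is independent of the IPS team and the same in both arms: for example the blinded researcher, the research nurse, or self-completion on Qualtrics, where the instruments already sit. Any lived-experience support should come from outside the IPS team and be offered alike in both arms. State that the two measures are completed before the follow-up qualitative interview. Then bring Table 2, the PROM and PREM section and the blinding section into agreement.

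If the investigators prefer to keep FEW involvement, the minimum is to state that these two measures are collected unblinded and to limit the single-blind statement to the research-nurse measures.

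The cost is a text edit and the reallocation of a task among existing staff. The downside is small: less support from an IPS peer worker while parents complete the forms.

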### Data collection and Management {18–19}

Research nurses who will be conducting the baseline assessment will be trained/ experienced in administering the study measures. All instruments will be uploaded into the Qualtrics platform for online surveys (www.qualtrics.com). For the measures requiring rating, more extensive training will be offered until raters achieve sufficient reliability.

#### Confidentiality {27}

All data collected will be kept securely and separate from any individual participant identifiers. Participants will be assigned a unique ID number to link their data throughout the trial.

### Statistical Methods {20A}

#### Quantitative Analyses

Descriptive statistics will be used to report the primary outcome of participant retention and recruitment. Retention will be presented as a simple percentage of participants randomised who remain in the study at 3/6-month end point. Recruitment will also be presented as a number, however, to capture movement through the research process, numbers and percentages will also be presented to summarise potential participants identified, invited, assessed for eligibility, eligible, and included and randomised into the study (Table 1). Data will also be presented for reasons for ineligibility, ambiguities regarding eligibility criteria, reasons for non-participation, and mode of assessment administration (face to face or remote). Reasons for exiting the study will be collected throughout the trial.

To supplement the process data of acceptability and feasibility of the outcome measures, the mean and standard deviations for the length of time taken for participants to complete baseline and follow-up assessments and errors and missing data will be captured. Comparisons will be made between face to face and remote assessments. For the putative outcome measures, the mean scores and standard deviations will be presented.

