		• Numbers and percentage of families interested, assessed for eligibility, meeting the inclusion criteria and included, of the total number identified	≥ 15 participants recruited per site, total 30 participants	**Amber**: If recruitment is below 30 families, adjust recruitment strategies or explore alternative pathways
		• Qualitative data on recruitment procedures and pathways (through interviews with the recruitment co-ordinator and professionals)	No criteria set	**Amber:** If significant barriers are identified, revise recruitment strategies or consider new outreach methods
	Participant eligibility	• Qualitative data on ambiguities regarding eligibility criteria, reasons for ineligibility and reasons for non-participation (through interviews with the recruitment co-ordinator and professionals)	No criteria set	**Amber**: Revise eligibility criteria or adjust strategies if significant ambiguities or issues are identified
	Randomisation	• Numbers and percentage successfully randomised at each trial site (target n15 at each site)	≥ 15 participants recruited per site, total 30 participants	**Green**: No adjustment needed if the target recruitment of 15 participants per site is met **Amber**: If randomisation sucess is lower than expected, revise recruitment or randomisation procedures
		• Qualitative data on participant understanding and acceptability of recruitment/ randomisation processes	No criteria set	**Amber**: Revise randomisation procedures or provide additional clarification if acceptability or understanding is low
Retention and attrition rates	Retention	• Number and percentage of families retained in the study for 3-6 months post randomisation	70% of participants retained at 3-6 months	**Green:** No adjustment needed if retention is at or above 70% **Amber:** If retention falls below 70%, explore reasons for attrition and adjust strategies (e.g., follow-up support) **Red**: If retention falls below 50%, review follow-up methods and consider additional participant engagement strategies
	Attrition	• Qualitative data on reasons for attrition (through interviews with the recruitment co-ordinator and professionals and quantitative data collected via online data management system)	No criteria set	**Amber:** If attrition is high, explore the reasons for attrition and revise follow-up methods or engagement strategies accordingly

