## Trial Design {8}

This multi-site single-blind randomised controlled trial (RCT) compares two services, IPS and SAU. The study will be a parallel, two-arm pilot RCT with a 1:1 allocation ratio across the two trial arms [1]. We will utilise a pre-post and 3/6-month follow-up design with embedded mixed-method process evaluation and exploratory economic analysis.

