### Sample Size {14}

We plan to recruit 30 families from Glasgow or London, with 15 families randomly allocated to IPS and 15 to SAU. Since the primary aim of this study is to assess recruitment rates, retention rates, and the acceptability of proposed measures, a formal power calculation is not appropriate. Our sample size was chosen to ensure a meaningful assessment of feasibility. If the true retention rate is 70%, the 90% confidence interval for this estimate will be approximately ± 15%, which we consider sufficiently precise for a feasibility study [97]. This level of precision allows us to make an informed decision about the feasibility of a larger trial. Additionally, as Hertzog (2008) [98] notes, the sample size for pilot studies should balance precision with logistical constraints, which we have considered in our planning. Furthermore, if the true retention rate is 70%, there is an > 80% probability that the observed retention rate will exceed 60%. If the observed retention rate falls below 60%, this would suggest that a future full-scale study is unlikely to be feasible without modifications. Even if feasibility is demonstrated, any future trial will include an internal pilot phase with close monitoring to ensure robust outcome data can be collected at scale.

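### Retention is judged on all randomised families together, so the Green rule can be met while one arm is below the protocol's own 50% Red line

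*Protocol article*

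**What the plan says.** The Sample Size section sets the numbers: "We plan to recruit 30 families from Glasgow or London, with 15 families randomly allocated to IPS and 15 to SAU". The Trial Design section describes a "parallel, two-arm pilot RCT with a 1:1 allocation ratio across the two trial arms".

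Under Quantitative Analyses the approach is descriptive: "Descriptive statistics will be used to report the primary outcome of participant retention and recruitment". The retention statistic itself is defined there as follows: "Retention will be presented as a simple percentage of participants randomised who remain in the study at 3/6-month end point".

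Table 1 (Objectives) attaches the decision to that figure. The Green entry reads "No adjustment needed if retention is at or above 70" (per cent). Amber applies below 70% and Red below 50%. No entry in the retention row refers to trial arm.

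The Sample Size section supports n = 30 by precision at 70% retention: "the 90% confidence interval for this estimate will be approximately ± 15%, which we consider sufficiently precise for a feasibility study". It adds that "there is an > 80% probability that the observed retention rate will exceed 60" (per cent).

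The Data Collection row of Table 1 sets no feasibility criterion for questionnaire completion. It has an Amber trigger if completion is low, without a number.

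**The concern.** The study is meant to show whether a trial comparing IPS with SAU can be run. For such a trial, unequal loss between the arms threatens the comparison in a way that the overall rate does not show. The protocol gives reason to expect that loss could be unequal: families know their allocation, and IPS families receive IPS, including contact with Family Engagement Workers, on top of usual services. A rule based only on the overall percentage cannot detect this in either direction.

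There is a second gap in the same statistic. Remaining in the study does not require that anything was measured. A family that never withdrew but gave no follow-up b-CAP, the planned principal measure for the definitive trial, could count towards Green.

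At stake is the message from the retention row. It could say that nothing needs changing when retention in one arm is poor enough to be Red if judged alone.

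**Working it through.** **Inputs.** N = 30, 15 per arm (Sample Size); Green at 70% or more, Red below 50% (Table 1); assumed retention 70% and a 90% interval of about ±15 points (Sample Size). The scenario of 90% against 50% is an assumption of this review.

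**1. The plan's own figures reproduce.**
- Wald half-width: 1.645 × √(0.7 × 0.3 / 30) = 13.8 points. With continuity correction, adding 1/(2 × 30), it is 15.4 points.
- Exact (Clopper-Pearson) 90% interval for 21/30: 53.5% to 83.4%, a mean half-width of 14.9 points.
- P(X ≥ 19 | n = 30, p = 0.7) = 0.841, which exceeds 80%.

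**2. Thresholds as counts.** Green overall: 0.70 × 30 = 21 or more. Below 50% in one arm: 0.50 × 15 = 7.5, so 7 or fewer.

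**3. What 21/30 can hide.**

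| Split | Arm rates | Exact 90% CI, higher arm | Exact 90% CI, lower arm | Lower arm under 50%? |
|---|---|---|---|---|
| 15 v 6 | 100% v 40% | 81.9–100% | 19.1–64.0% | yes |
| 14 v 7 | 93% v 47% | 72.1–99.7% | 24.4–70.0% | yes |
| 13 v 8 | 87% v 53% | 63.7–97.6% | 30.0–75.6% | no |

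At 22/30 (73%) the split 15 v 7 also leaves one arm under 50%. If one arm were lost entirely, the overall figure could be at most 15/30 = 50%, which is Amber.

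**4. Probability of Green.** Let A ~ Bin(15, p₁) and B ~ Bin(15, p₂) be independent. P(Green) is the sum of P(A = a)P(B = b) over a + b ≥ 21. With a floor f in each arm, the sum also requires a ≥ f and b ≥ f.

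| True retention | Rule as written | Floor 8/15 | Floor 9/15 |
|---|---|---|---|
| 70% v 70% | 0.589 | 0.586 | 0.566 |
| 75% v 65% | 0.589 | 0.583 | 0.549 |
| 80% v 60% | 0.590 | 0.568 | 0.497 |
| 90% v 50% | 0.593 | 0.454 | 0.294 |

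The rule as written gives almost the same chance of Green in every row, because the mean retention is 70% throughout.

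**5. Precision by arm.** 90% Wald half-width at 70% and n = 15: 1.645 × √(0.21 / 15) = 19.5 points. For the difference between arms: 1.645 × √(2 × 0.21 / 15) = 27.5 points.

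**The case against.** Several points on the other side stand.

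- Tabulation by arm and interval reporting are usual content of an analysis plan, and the article excludes neither. The absence of the 90% interval from the analysis text is therefore not a finding in itself. The decision rule is different: Table 1 states it, and an extra table elsewhere would not change what Green means.
- Green applies to one row only. The attrition row collects reasons for loss and has an Amber trigger if attrition is high, and the row on engagement with IPS and SAU has its own. The study does not lead directly to a larger trial, and any later trial would have an internal pilot. These soften the consequence, but none of them sets a condition on retention by arm.
- Missing questionnaires do have an Amber trigger, so the measurement gap is only partial. It remains because the trigger has no number and the retention count does not depend on it.
- At 15 per arm a hard gate is partly a matter of preference. With 70% true retention in both arms, at least one arm falls below 9/15 with probability 0.245. The benefit of a floor is also small when the true gap is moderate, as the 80% v 60% row shows.

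A reader might infer that Green is possible even if an arm is lost completely. It is not, since 50% overall is Amber. A reader might also infer that SAU families would be the ones to leave. That is plausible, but the documents do not say so, and the argument does not need it.

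**Conclusion.** The concern holds in a limited form. The retention statistic and the Green rule use overall retention only, and a severe imbalance between arms can satisfy the rule: 15/15 v 6/15, 14/15 v 7/15 or 15/15 v 7/15. Under an assumed 90% v 50%, Green is as likely (0.593) as under a uniform 70% (0.589).

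These probabilities assume exactly 15 families per arm and independent outcomes between families. They illustrate what the rule cannot see and do not predict that attrition will be unequal. The precision and probability stated in the Sample Size section are correct. The definition of retained is a smaller, related weakness.

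**What to change.** 1. In the Quantitative Analyses section, report retention overall and by randomised arm as n/N and percentage, each with an exact 90% interval.
2. In the retention row of Table 1, do not read the result as Green when either arm alone is below the protocol's own 50% line (fewer than 8/15). Treat this as an Amber flag that prompts a look at reasons for loss by arm, not as a formal comparison.
3. For this criterion, count a family as retained only if follow-up outcome data were obtained, namely the b-CAP.

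**Cost.** The change needs a few lines of analysis text and one table cell, with no new data collection. Under a uniform 70% the chance of Green falls from 0.589 to 0.586. A stricter floor of 9/15 would separate the 90% v 50% scenario better (0.294 instead of 0.454), but lowers the uniform-70% figure to 0.566. Arm-level intervals will be wide, about ±19.5 points at 70%, and should be read as such. Item 3 can only lower the retention count; by how much cannot be worked out from the documents.
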